### 2.3. Randomization of Subjects

Eligible patients recruited by nursing will be randomized as they are referred for physiotherapy treatment by the supervisor of the Physiotherapy Unit to one of the two trial groups after signing the informed consent. The sequence will be performed randomly in a 1:1 allocation to the Immersive VR training group and the Bayouk, Boucher and Leroux physical therapy training group for balance, using a computerized random allocation program.

This sequence will be prepared by an investigator not involved in the allocation of patients. 

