### 2.2. Participants

Eligible patients who agree to participate will meet the following inclusion criteria: Adults older than 18 and younger than 80 years old, with a diagnosis of stroke with hemiparesis or hemiplegia post-acute stroke admitted to hospital, and with a minimum score of 2 points in item 3.2 of the BBS (Berg Balance Scale) [41], which establishes that the patient can remain seated for 30 s without help. Exclusion criteria include aphasia, scores greater than 45 on the Mississippi Aphasia Screening Test [42]; cerebellar pathology; hemineglect or previous neurological disorder; visual disorders that prevent the use of VR glasses; moderate cognitive impairment, scores less than 24 on the MMSE (Mini-mental State Examination) [43]; previous musculoskeletal disorders that hinder or prevent balance in sitting and standing or gait; vestibulocochlear disease; spinal cord injury or disease; systemic peripheral neuropathy; persistent phobic postural dizziness; migraine; Ramsay Hunt Syndrome; and psychiatric disorders. 

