### 2.4. Intervention Protocol/Procedure

Eligible subjects will be identified by the stroke diagnosis; they will be patients admitted to the Neurology Service of the Miguel Servet Hospital in Zaragoza. In an initial visit, the nursing staff will inform those potentially eligible, who will be pre-selected based on whether or not they meet the inclusion and exclusion criteria for this study. Likewise, they will proceed to explain this study to the included subjects, collect the willingness to participate and provide the informed consent document.

Prior to random assignment, two physiotherapists who are experts in neurological assessment will evaluate the outcome variables for each participant. Subsequently, patients will be randomly assigned to the control group or the experimental group in a 1:1 ratio, computerized random assignment program. The patient will be informed that in subsequent evaluations, they do not reveal to the evaluators to which group they have been assigned.

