### 2.6. Intervention

Table 1 shows the treatment for each patient, which will be 30 min, 5 days a week.

The first part of the treatment, lasting 15 min, will be common to both groups and will be focused on the function of the structures; the following exercises will be prescribed for the flexor muscles of the upper limbs and the extensor muscle group of the lower limbs [44]:-Stretching exercises lasting 30 s each, with a maximum duration of 5 min;-Joint mobilization exercises of the hip, knee and ankle of both lower extremities, which will be carried out passively and with a total duration of 5 min;-Exercises for the active mobilization of the spine (flexion, extension, turning, etc.) with a maximum duration of 5 min.

The design of the second part of the treatment protocol will depend on whether the subjects are assigned to the control group or the Immersive VR intervention group (experimental group).

In the control group, this part of the treatment will be based on a static balance training program that has demonstrated its effectiveness; therefore, some of the exercises proposed by the authors Bayouk, Boucher and Leroux in their study have been used [39]. The exercises included in the intervention and their progression will depend on the initial situation of the participant. These exercises are shown in Table 2 and must be performed with opened and closed eyes on a hard and soft surface. 

In the experimental group, this second part will be a training program of static and dynamic balance in sitting and standing through Immersive VR. The application of Immersive VR is carried out through a Google device that has an application installed on the “FisioVR” device (Abaco Digital, Zaragoza, Spain), with dynamic and static experiences associated with different postural tasks in a realistic 360° environment. It is based on the need for people to receive treatment with the greatest freedom of movement that this device provides, as they are connected to the computer via Wi-Fi. Scenes are integrated in which they can start both standing and sitting in urban environments performed by photogrammetry and 360-degree spherical imaging, and, most importantly, it allows the patient to move and explore the environment.

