The designed scenarios recreate realistic environments for their recovery (Figure 2a,b). The patient must interact in the different sessions with 5 proposed scenarios (Figure 3). In these scenarios, they must solve double-task situations. On the one hand, the postural task using different positions in sitting, standing or walking, and on the other, the cognitive task using different elements within the scenarios (visual, arithmetic and auditory). Patients will progress in difficulty as their functional capacity allows, beginning with the sitting position and ending with ambulation. At the end of the sessions, they must go through all the positions, holding each position for 5 min.

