### 2.11. Data Management and Statistical Analysis

Sample size: For instance, to achieve 80% power to detect differences in contrast to the null hypothesis H₀, mean difference in BESTest is equal to the limit of superiority, using a one-sided Student’s t-Test (superiority) for two independent samples, taking into account that the significance level is 5%, and assuming that the superiority limit is 7.81 units, as suggested in the article by Candance, et al., [55]. Additionally, the proportion of patients in the control group with respect to the total is 50%; it will be necessary to include 18 patients in the control group and 18 in the experimental group, a total of 36 patients in this study. Considering that the expected percentage of dropouts is 20%, it would be necessary to recruit 22 patients in the control group and 22 patients in the experimental group, a total of 44 patients in this study.

Patient characteristics and comparisons at baseline: To assess the comparability of the two groups, the characteristics of the patients assigned to each group will be presented in a table. Discrete variables will be summarized as frequencies and percentages. Continuous variables and time intervals will be summarized using means, standard deviation, or median and interquartile range. Both groups need to be homogeneous at baseline.

The statistical analysis will be carried out by an intention-to-treat analysis.

Analysis of the main objectives: Normality tests of the dependent variables were undertaken using the Kolmogorov–Smirnov test. The description of the results of the dependent variables was also performed, using either the mean and the standard deviation or the median and interquartile range, depending on the adjustment of these variables to normality. 

To respond to the main objective, with each primary result, hypothesis tests will be performed (where the alternative hypothesis is the greater efficacy of the experimental treatment compared to the conventional one), and estimates will be provided by 95% confidence intervals. In addition, the t-Student test will be used for independent samples in the parametric case and the Mann–Whitney U test for the non-parametric case.

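### Allocation of 44 patients of very mixed function is described without a stratification factor and the primary test is unadjusted, so an avoidable chance imbalance and loss of precision remain

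*Protocol article*

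**What the plan says.** **Who enters.** Section 2.2 sets the functional floor at a score on one Berg Balance Scale item, "which establishes that the patient can remain seated for 30 s without help". It states no upper functional limit.

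**What range is expected.** In section 2.6 the virtual reality patients progress in difficulty, "beginning with the sitting position and ending with ambulation". For the control arm the same section says: "The exercises included in the intervention and their progression will depend on the initial situation of the participant". Table 3 schedules the TUG and the 10 m walk test at baseline as well as at 15 and 30 sessions.

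**How patients are allocated.** Section 2.3 states: "The sequence will be performed randomly in a 1:1 allocation to the Immersive VR training group and the Bayouk, Boucher and Leroux physical therapy training". It adds that this is done "using a computerized random allocation program". Section 2.4 repeats the computerised 1:1 assignment. Neither section names strata, blocks or minimisation.

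**What is known before allocation.** Section 2.4: "Prior to random assignment, two physiotherapists who are experts in neurological assessment will evaluate the outcome variables for each participant".

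**What is wanted and how it is analysed.** The baseline paragraph of section 2.11 ends: "Both groups need to be homogeneous at baseline". For the main objective the same section names the independent-samples t-test or, in the non-parametric case, the Mann-Whitney U test. It names no baseline covariate.

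**The concern.** Function at entry is likely to be strongly related to every balance and gait score, and it also decides which exercises a patient can do. The article expects a wide range of function, measures it before assignment and wants the arms to be alike. Yet neither the stated allocation nor the stated primary test uses that measurement.

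Two things are at stake in a sample of 44. First, an unlucky split of patients who can and cannot walk would be carried uncorrected into the primary comparison. The balance and gait scales depend on the same underlying function, so they would tend to move together, and the agreement could look like corroboration. Second, the spread between functional levels stays in the error term of an unadjusted test, which costs precision even when the split happens to be even.

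**Working it through.** **Inputs from the article (section 2.11).** 18 patients per arm before dropout and 22 per arm (44 in all) after it; one-sided 5% level; 80% power; 7.81 BESTest units.

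**Inputs assumed.** The share unable to walk at entry, the BESTest gap between the two functional levels, and the standard deviation (SD). The article gives none of these, so ranges are used.

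**1. The article's own figure.** Without an SD, 18 per arm cannot be reproduced directly. Taking 7.81 as the difference to be detected and solving for the SD with the normal approximation:

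SD = 7.81 / (1.645 + 0.842) × √(18/2) = 9.4

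The exact one-sided t-test gives 9.2. The total of 44 is taken as stated; stratification does not change it.

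**2. Chance imbalance with a 22:22 split.** Let K of the 44 patients be unable to walk. The number X of them in one arm is hypergeometric:

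P(X = x) = C(K, x) · C(44 − K, 22 − x) / C(44, 22)

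The difference between arms in the share unable to walk is |2x − K| / 22. The table gives the smallest attainable difference of at least 20 percentage points and the two-sided probability of that split or worse.

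| Unable to walk | Split or worse | Difference in share | Probability |
|---|---|---|---|
| 11 (25%) | 8 to 3 | 5/22 = 23 points | 2 × (0.0642 + 0.0150 + 0.0019 + 0.0001) = 0.16 |
| 15 (34%) | 10 to 5 | 5/22 = 23 points | 2 × (0.0741 + 0.0224 + 0.0043 + 0.0005) = 0.20 |
| 22 (50%) | 14 to 8 | 6/22 = 27 points | 2 × (0.0486 + 0.0138 + 0.0027 + 0.0003) = 0.13 |

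The SD of the difference in share is 13 to 15 points. If the program uses simple randomisation, so that arm sizes also vary, simulation gives about 14% (25% share) and 18% (50% share) for 20 points or more.

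**3. What an imbalance would do to an unadjusted comparison of final BESTest scores.** Shift = imbalance × gap. With a 20-point imbalance and assumed gaps of 10, 20 and 30 BESTest points:

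- 0.20 × 10 = 2 points
- 0.20 × 20 = 4 points
- 0.20 × 30 = 6 points

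These stand against the 7.81 units in section 2.11.

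**4. Precision.** Suppose the SD implied in step 1, about 9.3, is the spread within a functional level, and a share f is unable to walk. The total SD is then √(9.28² + f(1 − f) × gap²). Power of the unadjusted one-sided t-test at 18 per arm:

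| Gap | Total SD, f = 0.25 | Total SD, f = 0.50 | Power |
|---|---|---|---|
| none | 9.3 | 9.3 | about 80% |
| 10 | 10.2 | 10.5 | 70% to 73% |
| 20 | 12.7 | 13.6 | 52% to 57% |
| 30 | 16.0 | 17.6 | 37% to 42% |

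If 9.3 is instead the total SD, planned power is not reduced, and adjustment would raise it above 80%. Either way the unadjusted test is the less precise one.

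**5. With stratification.** With permuted blocks of 4 in two strata, the arms differ by at most 2 patients per stratum: 2/22 = 9 points.

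**The case against.** **Unstratified 1:1 allocation is sound.** This stands. It is valid and unbiased on average, and the error rate and the confidence interval already allow for chance imbalance. A reader might infer that the comparison is biased; the article does not support that. The weakness lies in balance within one small sample and in precision.

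**The article never says the sequence is unstratified.** This also stands. It describes the method in two places without a stratification factor, and a fuller protocol, not shown, might hold one. The point is therefore about the method as described.

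**The homogeneity sentence belongs to the baseline table.** A reader might take it as a design guarantee that section 2.3 contradicts. It closes a paragraph on describing comparability and sets no threshold and no consequence. It is a stated wish, and no allocation scheme, including one binary stratum, could guarantee it.

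**An imbalance could be repaired afterwards.** Correct: adjustment for the baseline score needs no stratification, and every scale in Table 3 is measured at T0. It would be wrong to say that nothing could be done. What remains is that the primary tests named in section 2.11 contain no such adjustment.

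**The harm is not certain.** The aim at the end of the Introduction speaks of change in the measures, and section 2.11 does not say whether final or change scores are tested. With change scores, an excess of non-walkers need not push all outcomes one way. The shifts in step 3 apply to final scores.

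**The probabilities depend on assumptions.** They do. With 22 non-walkers, 13 to 9 or worse occurs in 37% of trials, but that figure needs a 50% share and counts an 18-point difference. At a fixed difference of six patients or more, the probability falls from 13% with 22 non-walkers to 4.5% with 13 and 3.4% with 11. The 20-point criterion is used here across the whole assumed range.

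**Conclusion.** The point holds as an inexpensive improvement to a valid design. As described, baseline function is balanced neither by the allocation nor by the primary analysis, although the range is wide and the measurement exists before assignment.

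The size is a chance of about 13% to 20% that the arms differ by 20 percentage points or more in the share unable to walk. This rests on an assumed share of 25% to 50% and a 22:22 split. The effects on the BESTest difference and on power rest further on assumed gaps and on how the unstated SD is read, so they show the order of magnitude only. That walkers enter is itself an inference, drawn from the absent ceiling, the progression to ambulation and the baseline walking tests; it is not an entry criterion.

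**What to change.** **Section 2.3.** Stratify the computerised sequence on one binary factor from the pre-randomisation assessment: able or unable to complete the TUG or 10 m walk test. Use permuted blocks within each stratum.

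**Section 2.11.** Include that factor or, better, the baseline value of the outcome in the primary comparison, for example by ANCOVA. Stratifying without this step improves balance but does not recover the precision. Reword the homogeneity sentence as a description of comparability.

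**If allocation has already begun.** Leave the sequence as it is and make the baseline adjustment, which gives most of the gain. If the full protocol already stratifies, state the factor in 2.3 and carry it into the analysis.

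**Cost.** Two lists instead of one in the same program, with the sample size unchanged at 44. The one downside is that the baseline walking result must be available when the patient is allocated; section 2.4 already places that assessment before assignment.

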### 2.4. Intervention Protocol/Procedure

Eligible subjects will be identified by the stroke diagnosis; they will be patients admitted to the Neurology Service of the Miguel Servet Hospital in Zaragoza. In an initial visit, the nursing staff will inform those potentially eligible, who will be pre-selected based on whether or not they meet the inclusion and exclusion criteria for this study. Likewise, they will proceed to explain this study to the included subjects, collect the willingness to participate and provide the informed consent document.

Prior to random assignment, two physiotherapists who are experts in neurological assessment will evaluate the outcome variables for each participant. Subsequently, patients will be randomly assigned to the control group or the experimental group in a 1:1 ratio, computerized random assignment program. The patient will be informed that in subsequent evaluations, they do not reveal to the evaluators to which group they have been assigned.

### 2.5. Physiotherapists Training

The interventions in both groups will be carried out by 4 physiotherapists with at least 5 years of experience in patients post-stroke management. In addition, physiotherapists will attend a 2 h training session to improve the standardization of interventions and receive a detailed procedure for each intervention to ensure they are managing patients according to trial protocols as well as recording adverse events if required. 

### 2.6. Intervention

Table 1 shows the treatment for each patient, which will be 30 min, 5 days a week.

The first part of the treatment, lasting 15 min, will be common to both groups and will be focused on the function of the structures; the following exercises will be prescribed for the flexor muscles of the upper limbs and the extensor muscle group of the lower limbs [44]:-Stretching exercises lasting 30 s each, with a maximum duration of 5 min;-Joint mobilization exercises of the hip, knee and ankle of both lower extremities, which will be carried out passively and with a total duration of 5 min;-Exercises for the active mobilization of the spine (flexion, extension, turning, etc.) with a maximum duration of 5 min.

The design of the second part of the treatment protocol will depend on whether the subjects are assigned to the control group or the Immersive VR intervention group (experimental group).

In the control group, this part of the treatment will be based on a static balance training program that has demonstrated its effectiveness; therefore, some of the exercises proposed by the authors Bayouk, Boucher and Leroux in their study have been used [39]. The exercises included in the intervention and their progression will depend on the initial situation of the participant. These exercises are shown in Table 2 and must be performed with opened and closed eyes on a hard and soft surface. 

In the experimental group, this second part will be a training program of static and dynamic balance in sitting and standing through Immersive VR. The application of Immersive VR is carried out through a Google device that has an application installed on the “FisioVR” device (Abaco Digital, Zaragoza, Spain), with dynamic and static experiences associated with different postural tasks in a realistic 360° environment. It is based on the need for people to receive treatment with the greatest freedom of movement that this device provides, as they are connected to the computer via Wi-Fi. Scenes are integrated in which they can start both standing and sitting in urban environments performed by photogrammetry and 360-degree spherical imaging, and, most importantly, it allows the patient to move and explore the environment.

The designed scenarios recreate realistic environments for their recovery (Figure 2a,b). The patient must interact in the different sessions with 5 proposed scenarios (Figure 3). In these scenarios, they must solve double-task situations. On the one hand, the postural task using different positions in sitting, standing or walking, and on the other, the cognitive task using different elements within the scenarios (visual, arithmetic and auditory). Patients will progress in difficulty as their functional capacity allows, beginning with the sitting position and ending with ambulation. At the end of the sessions, they must go through all the positions, holding each position for 5 min.

### 2.7. Outcomes

All study participants will be evaluated before starting treatment (baseline) at 15 sessions and 30 sessions. The outcome measures are compiled in Table 3. 

The parameters of balance in sitting and standing static and dynamic and in the temporospatial and kinematic parameters of gait will be obtained from the following tests and scales. 

For static balance and functional mobility, the PASS Spanish version [21,45], the BBS [34] and the BESTtest [46] have been used. 

BBS has a high relative reliability with interrater reliability estimated at 0.97 (95% CI 0.96 to 0.98) and intra-rater reliability estimated at 0.98 (95% CI 0.97 to 0.99). The absolute reliability of the BBS varies across the scale, with minimal detectable change with 95% confidence varying between 2.8/56 and 6.6/56 [41].

PASS is a 12 items performance-based scale used for assessing and monitoring postural control following a stroke. It consists of a 4-point scale where three items are scored from 0 to 3, and the total scoring ranges from 0 to 36 [45]. The minimal detectable change in subacute stroke is 2.22 points [47]; in acute stroke, 1.8 points [48]; and in chronic stroke, it is 3.2 points [49].

BESTest consists of 27 tasks, with 36 items in total. Each item is scored based on ordinal scale scoring from 0 to 3, where 3 represents best performances, and 0 represents worst performances. Scores for the total test are provided as a percentage of total points [50]. Additionally, the minimal detectable change in subacute stroke is 7.81 points [50]. 

To measure dynamic balance and gait, the TUG test [51] and the 10 m walk test [52] will be used. 

In the TUG test, the patient rises from a chair, walks three meters in a straight line, turns, returns and sits down while the examiner times the time required to perform the test. In addition, the TUG assesses the risk of falling. A score of less than 10 s indicates a low risk of falling, between 10 and 20 s indicates frailty with a higher risk of falling, and more than 20 s a high risk of falling [51]. The minimum detectable change in stroke is estimated at 2.9 s [53].

10 m walk test has an excellent interrater reliability estimated ICC = 0.87 to 0.88, and an excellent interrater reliability ICC = 0.998. The minimum detectable change is set at 0.05m/s, and a substantial change is set at 0.10m/s [52].

The secondary outcomes will be measured with the following tools: quality of life with the ECVI-38 [54] and the adverse effects with a notebook for recording if they happen derived from the treatment.

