### 2.10. Data Collection Methods

The outcome measures set out below will be obtained prior to the intervention, at 15 sessions and 30 sessions, except for the sociodemographic and descriptive variables of the subject, which are reflected in Table 5.

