Analysis of the secondary outcomes: For quality of life, contrasts of hypotheses will be made, and estimates will be provided by a 95% confidence interval. Furthermore, it is of interest to establish a regression model between quality of life and static balance, functional mobility, dynamic balance and gait in order to estimate their possible relationships. The strength of these relationships will be measured through the ANOVA F-test and the individual t-test. The strength of the relationship will be expressed as ORs and their 95% CI.

This project takes into account qualitative information to explore the reasons for possible dropouts through direct follow-up of patients.

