**Figure 3 healthcare-11-01335-f003:**
[figure not shown]
Immersive Virtual Reality scenarios.

**Table 1 healthcare-11-01335-t001:** Protocol of intervention.

Intervention Protocol	
Control Group (CG)	Intervention Group (IG)
15 min: physiotherapy treatment aimed at achieving functional improvement and increased postural control [44].	15 min: physiotherapy treatment aimed at achieving functional improvement and increased postural control [44].
15 min: static and dynamic balance training in sitting and standing according to Bayouk, Boucher and Leroux protocol [39].	15 min: static and dynamic balance training in sitting and standing through Immersive VR.

**Table 2 healthcare-11-01335-t002:** Exercises of the protocol of Bayouk, Boucher and Leroux (control group).

Exercises	Repetitions	Total Time
Stand with feet together for 10 s.	8 repetitions	2 min
Hold the tandem posture for 10 s.	8 repetitions	2 min
Get up from the chair without using arms.	3 sets of 8 repetitions	3 min
Walk forwards and backwards with one foot in front of the other.		5 min
Stay in monopodal support for 10 s.	10 repetitions	3 min

**Table 3 healthcare-11-01335-t003:** Outcomes measures.

Outcome Domain	Measures Instrument	T0	T1	T2
Sociodemographic and descriptive data	Ad Hoc questionnaire	X		
Primary outcomes				
Static balance and functional mobility	PASS	X	X	X
	BESTtest	X	X	X
Dynamic balance and gait	10 m walk test	X	X	X
	TUG	X	X	X
Secondary outcomes				
Quality of life	ECVI-38	X	X	X
Adverse effects	Open questions		X	X

T0 baseline, T1 evaluation at 15 sessions, T2 evaluation at 30 sessions. PASS- Postural Scale for Stroke Patients; TUG- Timed Up and Go; BESTest- Balance Evaluation System Test; ECVI-38- Quality of life scale for stroke.

**Table 4 healthcare-11-01335-t004:** Study period: Schedule of enrollment, interventions and assessments of this study.

STUDY PERIOD					
	Enrolment	Allocation	Post-Allocation		Closeout
Time points baseline	t	0	t15	t30	tx
Enrollment					
Eligibility screen	X				
Informed consent	X				
Allocation		X			
Assessments					
Baseline variables		X			
Post. Intervention and follow-up variables			X	X	X
Interventions					
IVR training group			X	X	
Physical therapy with Bayouk, Boucher and Leroux exercises			X	X	

IVR: Virtual Reality intervention group.

**Table 5 healthcare-11-01335-t005:** Collection of sociodemographic and descriptive data.

**Sociodemographic and descriptive data**	Age	Years
	Gender	Male/female
	BMI	Underweight/normal weight/overweight

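### T1 and T2 are set by sessions completed and not by time since randomisation, so assessment of patients who stop early or miss sessions is undefined and the intention-to-treat comparison is put at risk

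*Protocol article*

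**What the plan says.** The follow-up schedule appears in four places in the protocol article, and each uses session counts.

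- Section 2.7: "All study participants will be evaluated before starting treatment (baseline) at 15 sessions and 30 sessions".
- Section 2.10: "The outcome measures set out below will be obtained prior to the intervention, at 15 sessions and 30 sessions".
- Table 3, footnote: "T0 baseline, T1 evaluation at 15 sessions, T2 evaluation at 30 sessions".
- Table 4 has columns t15 and t30 and a closeout column tx. The row "Post. Intervention and follow-up variables" is marked in all three, and tx is not defined.

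The Abstract and the aim at the end of the Introduction also define the short and medium term as 15 and 30 sessions. Section 2.6 sets the frequency for both arms: "Table 1 shows the treatment for each patient, which will be 30 min, 5 days a week". No calendar time or visit window is written.

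On the analysis, section 2.11 says "The statistical analysis will be carried out by an intention-to-treat analysis". The primary comparison is a two-sample t test or a Mann–Whitney test. The sample size allows for 20% dropouts. For patients who drop out, the same section plans to "explore the reasons for possible dropouts through direct follow-up of patients"; it does not mention measuring their outcomes.

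**The concern.** The number of sessions completed is determined after randomisation and can be affected by the assigned arm. The Discussion expects immersion to strengthen adherence, so on the trial's own reasoning attendance may differ between arms. Tying the assessment to this quantity has two consequences.

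1. **Selection.** A patient who stops at session 20 never reaches the event that triggers T2. Unless someone decides otherwise on the day, the outcome is not collected. The patients with a T2 value are then those who kept attending, and they may differ between arms in ways that randomisation no longer balances.
2. **Unequal recovery time.** A patient who misses sessions reaches session 30 later. The population is hospitalised and post-acute, so recovery unrelated to treatment is plausible over these weeks. Neither two-sample test adjusts for the time of assessment.

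An analysis plan can say how missing values are handled. It cannot recover outcomes that were never collected or realign visits already made at different times, so the matter belongs to the visit schedule.

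**Working it through.** **Inputs.** From section 2.11: 18 evaluable patients per arm (36 in total), 22 recruited per arm (44 in total), 20% dropout. From section 2.6: 5 sessions a week. From section 2.7: assessments at 15 and 30 sessions. Attendance rates are not in the document; those below are assumptions.

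**Step 1: the plan's own recruitment figure.** 18 × (1 + 0.20) = 21.6, rounded up to 22 per arm, or 44 in total. This reproduces the stated figure. Dividing by 0.80 instead gives 22.5, or 23 per arm (46 in total). That difference is small and is not the point here.

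**Step 2: patients who may have no defined T2.** The planned margin is 44 − 36 = 8. Applying 20% to those recruited gives 44 × 0.20 = 8.8. So about 8 to 9 of 44 randomised patients may stop before session 30.

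**Step 3: calendar time to reach each session count.** Weeks = sessions ÷ (5 × attendance).

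| Attendance (assumed except full) | 15 sessions | 30 sessions |
|---|---|---|
| 100% | 15/5 = 3.0 weeks | 30/5 = 6.0 weeks |
| 90% | 15/4.5 = 3.3 weeks | 30/4.5 = 6.7 weeks |
| 75% | 15/3.75 = 4.0 weeks | 30/3.75 = 8.0 weeks |

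**Step 4: gap between arms at T2.** With equal attendance the gap is 0. If one arm attended at 100% and the other at 90%, it is 6.7 − 6.0 = 0.7 weeks. At 90% against 75% it is 8.00 − 6.67 = 1.3 weeks.

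**Step 5: direction.** If VR raises attendance, VR patients reach session 30 sooner and control patients are assessed later, with more time for spontaneous recovery. The timing effect then works against VR. Selection through dropout has no predictable sign: it depends on who stops in each arm and why.

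**Step 6: provisions for patients who stop.** Set side by side, section 2.7 includes all participants but sets their evaluations by session count. Section 2.11 promises analysis by intention to treat. Its only provision for dropouts concerns their reasons. Table 4 has an undefined closeout column, while Table 3 lists outcomes only at T0, T1 and T2. None of these fixes a time at which a patient who stops early is measured.

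**The case against.** The other side has several fair points.

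- **A reader might infer that patients who stop have no outcome and that intention to treat cannot be carried out.** The document does not support this. Section 2.7 speaks of all participants, dropouts are to be contacted directly, Table 4 has a closeout column, and nothing says that assessment ends when treatment ends. Patients can be analysed as randomised, with missing values handled by a stated method that an article may leave to the full protocol or analysis plan. What stands is narrower: nothing fixes when such patients are assessed.
- **A reader might infer that the primary test is a completers analysis.** No passage restricts it to completers, and a dropout allowance is ordinary in trials analysed by intention to treat. A completers analysis is a possible result of the schedule, not a stated plan.
- **A reader might turn the timing gap into BESTest points and set it against the 7.81 superiority limit.** That would multiply an assumed attendance gap by an assumed weekly recovery rate. The document gives neither, and the result would hide that the likely direction is against VR.
- **The anchor is partly deliberate.** The aim is framed by sessions received, and both arms follow the same 5-day week, giving nominal times of 3 and 6 weeks. This is true, and moving to calendar time does shift the question slightly. But the session-count question conditions on attendance, which sits badly with the intention-to-treat commitment.

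**Conclusion.** The point holds as a design weakness that is cheap to improve. Every dated follow-up depends on sessions completed, so T1 and T2 are undefined for patients who stop early and fall later for those who miss sessions. On the plan's own 20%, about 8 to 9 of 44 patients are affected by the first problem. Under assumed attendance of 90% and 75%, the second moves T2 from 6.0 weeks to 6.7 and 8.0 weeks.

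The size of any resulting bias cannot be derived from the document. The timing part vanishes with equal attendance. It would cost the trial power, and would not favour VR, if VR improves attendance as the Discussion expects. The selection part could go either way. The finding rests on the schedule as written in the article; if the full protocol already gives dates and covers patients who stop, only the wording needs aligning.

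**What to change.** - Schedule T1 and T2 at 3 and 6 weeks from randomisation (15/5 and 30/5 at the protocol's own frequency), with a stated window. This presumes that treatment starts promptly after allocation; the window should absorb short delays.
- State that every randomised patient is assessed at those times whatever the number of sessions attended, using the contact with dropouts that is already planned.
- Define the closeout point tx in Table 4 and say which outcomes are measured then.
- Report sessions attended by arm as adherence.

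This changes when outcomes are measured and leaves the treatment schedule alone. A baseline-adjusted mixed model over T1 and T2 would be a reasonable analysis, but it is a separate and optional choice; collecting the outcomes is what matters.

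**Cost.** Protocol wording, booking the same two assessments by date, and some effort to bring back patients who have stopped. The downside is that some patients are assessed after fewer sessions than intended, so the result is for the programme as offered and not for exactly 15 or 30 sessions. The short- and medium-term wording of the aim should be adjusted to match.
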